#### 7.1.3 Primary immunogenicity Endpoints

1. Etoricoxib effect of TB specific immunogenicity: T cell proliferation and cytokine responses (change between day 0 and 140)

2. H56:IC31 vaccine immunogenicity: T cell proliferation and cytokine responses 14 days post-immunization (day 98 and day 154 compared to day 84)
3. Etoricoxib effect of H56:IC31 vaccine immunogenicity: T cell proliferation and cytokine responses 14 days post-immunization compared to H56:IC31 alone.

#### **7.1.4 Exploratory immune studies**

Several functional immune assays will test time- and drug-dependent aspects of cellular immune responses to non-specific and specific stimuli. These tests will be carried out at the different partner sites with corresponding technologies (see 7.1.2, table 3).

## **7.2 Safety and Tolerability Assessments**

Safety will be monitored by the assessments described below as well as the collection of AEs at every visit. Significant findings that are present prior to the signing of informed consent will be included in the relevant medical history/ current medical condition page of the CRF. For details on AE collection and reporting see Section 8.

See Flow chart in Section 6 (table 2) for assessment schedule.

The “clinical investigational group”; the sponsor ([name]), the PI ([name]) and the clinical study investigators will review the safety data throughout the course of the study and report as stated in section 8.7.

#### **7.2.1 Medical History**

A summary of the patient's relevant medical history will be recorded on the appropriate CRF page(s). The following information will be collected:

- Diagnosis of co-morbidities (i.e diabetes, kidney failure), co-infections (HIV, Hepatitis B and C), incident events (i.e gastric ulcer, allergy, asthma) and previous TB.
- Time, duration, treatment and outcome of the respective diagnosis.

#### **7.2.2 Physical Examination**

A qualified physician will conduct a physical examination including an examination of general appearance, skin, neck (including thyroid), fauces, lymphoid glandels, eyes, lungs, heart, abdomen, basic nervous system evaluation, peripheral circulation.

Any pathological physical examination finding after start of treatment that is classified by the investigator as a clinically significant worsening compared to previous exam will be considered an AE, documented on the subject's CRF, and followed until the outcome is determined.

#### **7.2.3 Vital Signs**

To be measured: Body temperature, systolic/diastolic blood pressure, heart rate, weight.

Any vital sign value after start of treatment that is judged by the investigator as a clinically significant worsening compared to previous exam will be considered an AE, documented on the subject's CRF, and followed until the outcome is determined.

#### **7.2.4 Clinical Laboratory Evaluation**

The routine laboratory analyses will be performed at the Central Laboratory at Oslo University Hospital.

Haematology assessments will include the following parameters: haemoglobin, leucocytes, monocytes, lymphocytes, platelets, ESR.

Blood chemistry assessments will include the following parameter: CRP, Na, K, Ca, creatinine, creatinine-clearance, ASAT, ALAT, LDH, bilirubin, amylase, CK, gammaGT, cholesterol, glucose, HbA1C, urine acid. Serum-hCG and urine-hCG for females.

Results from clinical laboratory tests obtained as part of the study will be reviewed by a medically qualified study team member and treated in accordance with site policies.

Any laboratory value that is judged by the investigator as a clinically significant worsening compared to previous exam or has increased in toxicity grade after start of treatment with IMPs (see Appendix for toxicity grading scales) must be reported as an AE, documented on the subject's CRF, and followed until the outcome is determined.

The signed and interpreted laboratory results will be kept together with the subject's CRF as supplemental pages.

### **7.2.5 Pharmacokinetics**

The AUC and Cmax of etoricoxib at steady state after 7 days of treatment will be analyzed in Arm #1 in order to study the degree of interaction between etoricoxib and rifampicin. Blood samples will be collected in heparinized tubes at regular intervals during 96 hours as previously described (32). The blood samples will be protected from light and stored on ice until the plasma could be separated. The separated plasma was stored at -20°C until analysis for etoricoxib.

### **7.2.6 Radiology**

Routine chest X-ray or CT/PET scan will be performed at Dep. of Radiology, Oslo University Hospital before initiation of the study and at least at day 56 and day 182 and in addition according to clinical evaluation.

### **7.2.7 Adverse Events (AEs)**

The adverse drug reaction (ADR) profiles for etoricoxib give reason to expect gastrointestinal AEs, especially nausea, as the most common (see section 8.2). Headache may also occur. In addition, study personnel must remain vigilant for the occurrence of any event related to the patients' TB diagnosis and anti-TB chemotherapy where gastrointestinal ADRs are the most common as well as to all other types of AEs.

## **8 SAFETY MONITORING AND REPORTING**

The investigator is responsible for the detection and documentation of events meeting the criteria and definition of an adverse event (AE) or serious adverse event (SAE). Each patient will be instructed to contact the investigator immediately should they manifest any signs or symptoms they perceive as serious.

The methods for collection of safety data are described below.

### **8.1 Definitions**

#### **8.1.1 Adverse Event (AE)**

An AE is any untoward medical occurrence in a patient administered a pharmaceutical product and which does not necessarily have a causal relationship with this treatment.

An adverse event (AE) can therefore be any unfavorable and unintended sign (including an abnormal laboratory finding), symptom, or disease temporally associated with the use of a medicinal (investigational) product, whether or not related to the medicinal (investigational) product.

The term AE is used to include both serious and non-serious AEs.

If an abnormal laboratory value/vital sign are associated with clinical signs and symptoms, the sign/symptom should be reported as an AE and the associated laboratory result/vital sign should be considered additional information that must be collected on the relevant CRF.

All conditions that exist prior to administration of the study vaccine (pre-existing conditions) will be recorded in the subject's medical history to establish baseline. Day-to-day fluctuations in pre-existing conditions that do not represent a clinically significant change in the subject's status will not necessarily be reported as AE.

Any adverse change from the subject's baseline condition that occurs following the administration of the IMPs will be considered an AE. This includes the occurrence of a new AE or the worsening of a baseline condition, whether or not considered related to the IMPs. Intermittent conditions such as headaches may be present on Study Day 0 but may represent an AE if the intensity or duration of the event is worse than usual following receipt of IMPs. AE include, but are not limited to: adverse changes from baseline that represent increases in toxicity grade according to the Toxicity Table adverse changes in the general condition of the subject, signs and symptoms noted by the subject, concomitant disease with onset or increased severity and changes in laboratory safety parameters occurring after administration of IMPs.

### **8.1.2 Serious Adverse Event (SAE)**

Any untoward medical occurrence that at any dose:

- Results in death
- Is immediately life-threatening
- Requires in-patient hospitalization or prolongation of existing hospitalization
- Results in persistent or significant disability or incapacity
- Is a congenital abnormality or birth defect
- Is an important medical event that may jeopardize the subject or may require medical intervention to prevent one of the outcomes listed above.

Medical and scientific judgment is to be exercised in deciding on the seriousness of a case. Important medical events may not be immediately life-threatening or result in death or hospitalization, but may jeopardize the subject or may require intervention to prevent one of the listed outcomes in the definitions above. In such situations, or in doubtful cases, the case should be considered as serious. Hospitalization for administrative reason (for observation or social reasons) is allowed at the investigator's discretion and will not qualify as serious unless there is an associated adverse event warranting hospitalization.

### 8.1.3 Suspected Unexpected Serious Adverse Reaction (SUSAR)

Adverse Reaction: all untoward and unintended responses to an investigational medicinal product related to any dose administered;

Unexpected Adverse Reaction: an adverse reaction, the nature or severity of which is not consistent with the applicable product information.

Suspected Unexpected Serious Adverse Reaction: SAE (see section 8.1.2) that is unexpected as defined in section 8.2 and possibly related to the investigational medicinal product(s).

## 8.2 Expected Adverse Events (EAE)

**Etoricoxib**: Gastrointestinal EAE and headache are the most commonly occurring.  $\geq 1/100$  til  $< 1/10$ : abdominal pain, constipation, gastritis, reflux, gas, diarra, dyspeptic discomfort, nausea, vomiting, eosophagitis, palpitations, arrhythmia, hypertension, alveolar osteitis, increase in liver enzymes (ALAT/ASAT), bronchospasm, dizziness, headache, oedema, fatigue (text from Arcoxia, MSD, ATC-nr.: M01A H05 in Felleskatalogen). The EAEs will be recorded in the CRF.

**H56:IC31**: Vaccination with H56:IC31 has been associated most commonly ( $\geq 10\%$  of subjects with one or several of the AE) with mild to moderate injection site reactions of pain, warmth, and swelling, mild to moderate systemic adverse events of fatigue, bradycardia, myalgia, nausea, headache, arthralgia, and white blood cell count increased; and mild to severe hypertension (Table 5-8, page 72, Statens Serum Institut Investigator's Brochure).

There have been no suspected unexpected serious adverse reactions (SUSARs) reported to date in clinical trials of H56:IC31.

## 8.3 Disease Progression/Recurrence

Progression of TB disease during the study is not expected since only patients infected with drug sensitive *Mtb* isolates given appropriate anti-TB chemotherapy are included.

It is expected that some few patients could experience initial worsening of symptoms due to the nature of the TB disease. Events definitely explained as caused by TB, will not be reported as an AE/SAE. However, if the investigator considers that there is a causal relationship between the IMPs and the disease progression or increase in symptoms then this must be reported as an SAE.

Death due to progressive disease is to be recorded on a specific form in the CRF, but not as an SAE.

## 8.4 Time Period for Reporting AE and SAE

For each patient the standard time period for collecting and recording AE and SAEs will begin at baseline (day 0) when anti-TB chemotherapy and study drug etoricoxib are started and continue until day 238 (14 weeks after the last dose of etoricoxib and last H56:IC31 immunization is given).

For H56:IC31 specific AEs will be reported through 14 days after each vaccination, injection site assessments performed through 14 days after each vaccination and SAE and SUSARs reported until end of study. The monitor will review unblinded safety data and make a formal recommendation on the continued conduct of the trial after each safety review.

During the course of the study all AEs and SAEs will be proactively followed up for each patient; events should be followed up to resolution, unless the event is considered by the investigator to be unlikely to resolve due to the underlying disease. Every effort should be made to obtain a resolution for all events, even if the events continue after discontinuation/study completion.

## 8.5 Recording of Adverse Events

If the patient has experienced or hospital personnel have observed AEs the investigator will record the following information in the CRF:

Date and time of onset and resolution (duration), severity (defined below), the nature of the event described by the investigator in precise standard medical terminology (MedDRA Version 18.0), whether it required treatment or action taken, outcome, relationship to the patient's TB diagnosis or treatment and whether the AE caused withdrawal from the study.

The **severity** of all AE, including clinical findings and abnormal laboratory values will be classified as one of the following grades using the following definitions:

- |              |                                                                      |
|--------------|----------------------------------------------------------------------|
| 1) Mild:     | Tolerable                                                            |
| 2) Moderate: | Interferes with normal activity                                      |
| 3) Severe:   | Incapacitating (causes inability to perform usual activity or work). |

In addition, a Toxicity Table (*US FDA guidance: Toxicity Grading Scale for Healthy Adult and Adolescent Subjects Enrolled in Preventive Vaccine Clinical Trials, September 2007*) is provided in the protocol appendix for the grading of severity of specified AE. For AE not listed in the Toxicity Table determination of severity requires some level of interpretation as outlined above. The degree of incapacity caused by the AE and the level of medical intervention required for treatment may be helpful in assessing the overall severity of the AE.

The **causal relationship** of the event to the study medication will be assessed as one of the following:

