## Supplementary Table 10. Adverse events tables Day 85 to day 154 Safety Analysis Set\* (N=40)

### Summary of AEs

|                                                    | etoricoxib N=11 | H56:IC31 TB vaccine N=11 | Control N=10 | etoricoxib and H56:IC31 TB vaccine N=8 |
|----------------------------------------------------|-----------------|--------------------------|--------------|----------------------------------------|
| Any AE                                             | 7 (63·6%)       | 9 (81·8%)                | 5 (50·0%)    | 5 (62·5%)                              |
| Number of AEs                                      | 20              | 24                       | 15           | 15                                     |
| Number of SAEs                                     | 0               | 0                        | 0            | 0                                      |
| Number of SUSARs                                   | 0               | 0                        | 0            | 0                                      |
| One AE                                             | 1 (9·1%)        | 1 (9·1%)                 | 2 (20·0%)    | 3 (37·5%)                              |
| Two AEs                                            | 2 (18·2%)       | 4 (36·4%)                |              |                                        |
| Three or more AEs                                  | 4 (36·4%)       | 4 (36·4%)                | 3 (30·0%)    | 2 (25·0%)                              |
| Any treatment related AE                           | 4 (36·4%)       | 6 (54·5%)                |              | 3 (37·5%)                              |
| Number of AE leading to study drug discontinuation | 0               | 1 (9·1%)*                |              | 0                                      |

\* 1 patient registered with study drug interruption, but due to not receiving vaccine dose nr 2, the AE was re-categorized to “AE leading to study drug discontinuation”.

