## 5 TREATMENT

For this study the following are defined as Investigational Medicinal Product(s) (IMP).

- **Arcoxia®** blister tablets 120 mg.
- **H56:IC31** TB vaccine 5 µg

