### **6.3.2 Specific Rules for Discontinuing etoricoxib in an Individual Subject**

- An objective clinical or laboratory parameter change which meets Grade 3 or Grade 4 severity, as defined in the protocol toxicity table, AND is judged to be possibly, probably, or definitely related to etoricoxib.

- Deterioration in the patients condition which in the opinion of the Principal Investigator warrants study medication discontinuation (to be records as an AE or under Investigator Discretion).

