### **6.3.3 Rules for Discontinuing Vaccine Injections in an Individual Subject**

Administration of additional study injections will be discontinued for an individual subject if he/she has any of the following:

- An objective clinical or laboratory parameter change which meets Grade 3 or Grade 4 severity, as defined in the protocol toxicity table, AND is judged to be possibly, probably, or definitely related to study vaccine.
- Fever (oral temperature  $\geq 39^{\circ}\text{C}$ ) within 1 week following study injection which is associated with constitutional symptoms (myalgia, arthralgia, fatigue, headache, anorexia, hives, chills) AND is judged to be possibly, probably, or definitely related to study injection.
- Injection site reaction that involves severe induration ( $>10$  cm, prevents daily activity or necrosis/ulceration), erythema ( $>10$  cm or necrosis/ulceration/ exfoliative dermatitis), tenderness (significant discomfort at rest or study site visit or hospitalization) or pain (any use of narcotic pain reliever or prevents daily activity or study site visit or hospitalization).
- Any event that in the opinion of the principal investigator precludes administration of any further study injections.

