**Possible:**

There is reasonable causal relationship between the investigational product and the AE. Dechallenge information is lacking or unclear.

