### 8.7.2 SUSARs

SUSARs will be reported to the Norwegian Medicines Agency according to national regulation ("Forskrift om klinisk utprøving av legemidler til mennesker av 30.10.2009 (FOR-2009-10-30-1321)"). The following timelines should be followed:

The sponsor ([name]) will ensure that all relevant information about suspected serious unexpected adverse reactions that are fatal or life-threatening is recorded and reported as soon as possible to the Norwegian Medicines Agency in any case no later than seven (7) days after knowledge by the sponsor of such a case, and that relevant follow-up information is subsequently communicated within an additional eight (8) days.

All other suspected serious unexpected adverse reactions will be reported to the Competent Authority concerned as soon as possible but within a maximum of fifteen (15) days of first knowledge by the sponsor. SUSARs will be reported using in “paper form” or by the the CIOMS form since OUS is not connected to EudraVigilance.

Both SAEs and SUSARs related to the H56:IC31 will be reported to SSI within the same deadlines by cryptic e-mail [[contact]](mailto:[contact]) or fax.nr. [contact].

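### Section 8.5 specifies one causality rating per adverse event against the study medication, although arm 4 receives two investigational products and four protocol rules depend on relatedness to one named product

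*Protocol*

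**What the plan says.** Section 5 of the protocol names two investigational products, Arcoxia (etoricoxib) and H56:IC31. Under section 3, arm 4 takes etoricoxib from day 0 to day 140 and is vaccinated on days 84 and 140.

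Section 8.5 lists what is recorded for each AE. The causal relationship "of the event to the study medication will be assessed as one of the following", and five categories follow. They are worded for one product; Possible, for example, begins "There is reasonable causal relationship between the investigational product and the AE". The only other relationship item is the "relationship to the patient's TB diagnosis or treatment and whether the AE caused withdrawal from the study". Section 10.4.1 plans a summary of relationship to study drug, again in the singular.

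Other sections need an answer for a named product:

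- Section 5.5 (etoricoxib dose modification) and section 6.3.2 (stopping etoricoxib) apply when an event meets their severity condition "AND is judged to be possibly, probably, or definitely related to etoricoxib".
- Section 6.3.3 (stopping vaccine injections) applies when it does so "AND is judged to be possibly, probably, or definitely related to study vaccine".
- Section 8.7.2 states: "Both SAEs and SUSARs related to the H56:IC31 will be reported to SSI within the same deadlines".

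The results tables supplied with the protocol (Supplementary Tables 9 to 11) give one row, "Any treatment related AE", per arm and interval. They do not split it by product.

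**The concern.** A single rating fits arms 1 and 2, where only one product is given. In arm 4 after the first vaccination an event may be judged related to one product and not to the other, and the scale in section 8.5 has no place for two answers. Its categories also work differently for the two products. Unrelated covers a product that was not taken. Probable requires a response to dechallenge, which suits a daily tablet but not an injection already given. The term study medication adds to the ambiguity, because the visit descriptions in Appendix 6 use it for etoricoxib.

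Expectedness is affected too. Section 8.2 gives a separate list for each product, while the SUSAR definition in section 8.1.3 refers to the product or products together.

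The primary objective is the safety of etoricoxib alone and in combination with the vaccine. At stake is whether arm 4's related events after vaccination can be described by suspected product, and whether the record supports the four rules that need that judgement.

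**Working it through.** **1. The reported figures reproduce.** Participants with any treatment-related AE, n/N, from Supplementary Tables 9, 10 and 11:

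| Interval | Arm 1 (etoricoxib) | Arm 2 (H56:IC31) | Arm 4 (both) |
|---|---|---|---|
| Days 0-84 | 10/13 = 76.9% | 0/12 | 9/10 = 90.0% |
| Days 85-154 | 4/11 = 36.4% | 6/11 = 54.5% | 3/8 = 37.5% |
| Days 155-238 | 3/10 = 30.0% | 3/11 = 27.3% | 2/8 = 25.0% |

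All match the printed percentages. The arm 4 entries in the last two rows are those for which the suspected product is not identified.

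**2. How many arm 4 events timing settles.** Arm 4 AEs of any causality: 52 + 15 + 8 = 75. Before the first vaccination only etoricoxib has been given, and the first safety interval ends there.

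- Days 0-84: 52/75 = 69.3%.
- After day 84: 15 + 8 = 23, and 23/75 = 30.7%.

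The split is not perfectly clean, because the days 0-84 table lists 2 vaccination-site pain events in arm 4. Those two identify their own product.

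**3. How many of the 23 the event type settles.** Supplementary Table 10 lists for arm 4 one local reaction, one vaccination-site induration and two vaccination-site pain events: 1 + 1 + 2 = 4. That leaves 23 - 4 = 19, and 19/75 = 25.3%.

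**4. Whether the section 8.2 lists settle the 19.** Matching preferred terms to the two lists gives:

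- on both lists: nausea 1, fatigue 2, headache 1 = 4 (hypertension is on both lists but did not occur);
- on the etoricoxib list only: abdominal pain 1, dizziness 1 = 2;
- on the vaccine list only: arthralgia 1, myalgia 1 = 2;
- on neither list: lip ulceration 1, influenza-like illness 1, nasopharyngitis 1, wheezing 2, lymphadenopathy 3, aphthous ulcer 1, weight decreased 1, acne 1 = 11.

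Check: 4 + 2 + 2 + 11 = 19. A list match is a hint and not a causality judgement, so 19 stays an upper bound.

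**5. Whether stopping etoricoxib settles days 155-238.** It does not. Arm 1 receives only etoricoxib, and 3/10 of its participants have a related AE in that interval. Investigators were therefore still attributing events to etoricoxib after it had ended.

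The tables give related AEs as participants only, so the counts in steps 2 to 4 are for AEs of any causality. No sample size, power or error rate enters this point.

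**The case against.** Section 8.5 never says that only one judgement may be made, and the eCRF is not shown. Sections 5.5, 6.3.2 and 6.3.3 use the upper three levels of the section 8.5 scale for a named product, so the investigator must already judge each product for the events they cover. This stands in part. It cannot be claimed that product-level causality was never captured. But section 8.5 as written does not ask for it, and the reported tables do not show it.

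A reader might infer that arm 4's related AEs cannot be assigned to a product at all. The documents do not support that: 52 of the 75 AEs are in the interval before first vaccination, and 4 of the other 23 are local or vaccination-site events.

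A reader might also infer that arm 4 cannot be compared with arms 1 and 2. That is not supported either. For days 85-154, any AE occurred in 7/11, 9/11 and 5/8 participants in arms 1, 2 and 4, and the related rows stand side by side as well. Arm-level rates need no attribution by product. Section 3 recruits arm 4 only after the Group A safety review, so the comparison is not concurrent, but that is a separate limitation.

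The product-specific rules also had little to act on. After day 84 arm 4 had no SAE, no SUSAR, no severe AE and no AE leading to discontinuation, and all eight vaccinated participants received both doses. This stands and limits the practical harm in this trial.

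Finally, tabulation by product is detail that a statistical analysis plan may hold. This point therefore rests on what section 8.5 states and what the tables report, not on the absence of such detail.

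**Conclusion.** The point holds in limited form. Section 8.5 specifies one rating where four other provisions need one per product, and the reported related-AE rows for arm 4 after first vaccination (3/8 and 2/8) are pooled. The affected events are at most 19 of arm 4's 75 AEs (25.3%).

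This rests on three assumptions: that the singular wording of section 8.5 describes what was collected, that the interval tables place events correctly around the first vaccination, and that local and vaccination-site events are attributable to the vaccine.

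Overall safety comparisons between arms stay valid as descriptive summaries, and the primary objective is not blocked. What is missing is the product-level reading of systemic events in the combination arm. It is a modest gap and cheap to close.

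**What to change.** - In section 8.5, and in the eCRF if it does not already do so, record relatedness separately for etoricoxib and for H56:IC31, with a not-applicable entry where a product was not given. Record action taken for each product in the same way. This brings the recording into line with sections 5.5, 6.3.2, 6.3.3 and 8.7.2.
- Word the causality categories for each investigational product instead of the study medication.
- For arm 4 after first vaccination, tabulate related AEs and AEs leading to discontinuation by product.
- If the eCRF already holds product-level judgements, state this in section 8.5 and use them in the tables.

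The cost is two extra fields and the added table rows. For data already collected, at most 23 arm 4 events after day 84 would need a retrospective judgement. It would be made with knowledge of treatment and outcome, so it should be labelled as retrospective and open-label and given little weight. No dose or clinical rule changes.
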